### Models

#### Primary and secondary outcomes

Analyses of primary outcomes will be conducted among those fulfilling the respective criteria for inclusion at baseline, for example weekly alcohol consumption will be analysed among those who reported having consumed 10 or more drinks of alcohol in the past week. BMI and candy/snacks will be analysed among all participants, and number of cigarettes smoked weekly among baseline smokers.

Weekly alcohol consumption, frequency of heavy episodic drinking per month, weekly intake of candy and snacks, number of sugary drinks per week, and cigarettes smoked per week are all count variables that are likely skewed and overdispersed. Therefore, these outcomes will be analysed using negative binomial regression. If found not to be overdispersed, we will consider using normal regression (possibly log transformed). Average intake of fruit and vegetables per day, MVPA minutes per week, and BMI will be analysed using normal regression (possibly log transformed). Point prevalence of smoking abstinence will be analysed using logistic regression.

All models will be adjusted for sex, age, family’s economic situation, and mediator variables at baseline. Effect modification will be investigated by estimating the outcome models with interaction terms for each baseline variable respectively. To further investigate effect modification with respect to socioeconomic status, we will estimate the outcome models with both education and economic status as interaction terms. A final effect modification model will be estimated with a binary interaction variable representing age being greater to or equal to 18 (ie. drinking age).

#### Mediator outcomes

Mediators will be explored using a causal inference framework [58, 59], where Monte Carlo methods are relied upon for inference. This allows for any type of model (linear and nonlinear) to be used to represent the relationships between the group allocation, mediating variable, and the outcome. Four models will be created for each primary outcome, three which investigate the mediating factors on their own, and a fourth which incorporates all mediators at once. If any baseline characteristics are found to moderate the effect in the primary analysis, then additional mediator models will be created to include these as moderators.

### Exploratory outcomes

#### Interactions among lifestyle change

Outcome interactions, and determinants of such, will be investigated in an exploratory analysis. For instance, those who quit smoking may also be more likely to reduce their alcohol consumption, and this interaction may be moderated by baseline characteristics. Models to detect such interactions will be explored and findings will be used to create hypotheses for future research.

#### Protective effects of the intervention

The primary analyses are all done among those presenting with particular health risk behaviours at baseline, however, all participants will receive the same multiple lifestyle intervention, thus it is possible that the intervention may protect participants from developing unhealthy behaviour. To investigate this we will, for each primary outcome, contrast all participants in the intervention and control groups to assess if either group is more or less likely to develop unhealthy risk behaviours over the intervention period.

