### Study setting, recruitment and eligibility

Participating high schools (approximately 300 high schools with approximately 80,000 students in total) will recruit students to the trial using: printed advertising (posters and leaflets), digital advertising (email, school website, app), and school staff (teachers, mentors, and/or school health centers). Participants will initially be recruited over a 6-month period, with additional 3-month periods added until the required number of participants has been reached (see Power Calculations). Recruitment will not extend past 24 months, regardless of number of participants recruited, and will commence in September 2020.

Students will register their interest by sending a text message to a dedicated telephone number (included in all information materials). In response, students will receive a text message with a hyperlink to a web page presenting trial information and will be asked to give informed consent to participate. All students who consent will immediately be asked to complete an online baseline questionnaire (see Additional file 1), which will also be used to assess eligibility for the trial.

Students will be included in the trial if they fulfil at least one of six conditions, which are related to the primary outcomes of the trial. The conditions are:
**Weekly alcohol consumption:** Consumed 10 or more standard drinks of alcohol the past week. A standard drink of alcohol is in Sweden defined as 12 g of pure alcohol.**Heavy episodic drinking:** Consumed 4 or more standard drinks of alcohol on a single occasion at least once in the past month.**Fruit and vegetables:** Consumed less than 500 g of fruit and vegetables on average per day the past week.**Sugary drinks:** Consumed 3 or more units of sugary drinks the past week. One sugary drink unit is defined as approximately 33 cl.**Moderate to vigorous physical activity:** Spent less than 420 min on moderate to vigorous physical activity in the past week (ie. approximately 60 min per day).**Smoking:** Having smoked at least one cigarette the past week.

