#### Randomisation

Block randomisation using random selection of block sizes of 2 and 4 will be used to ensure 1:1 randomisation without creating risk for revealing the allocation sequence. All randomisation sequences will be computer generated and allocation will be automatically done by the backend system. While research personnel will be blind to participant allocation, participants will be aware of which condition they receive, thus the trial will be single blinded.

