#### Power calculations

Considering the novelty of the intervention (digital multiple lifestyle) and the population (Swedish high school students), there are no existing full-scale trials from which an estimate of effects can be assumed. Also, as there are no interventions of this type available to high school students in Sweden, minimal relevant effect sizes were considered for this trial. We have based expected effect sizes on what we believe are minimally relevant for the population, and reasonable, given the target population and digital intervention context. For those included based on weekly alcohol consumption, who drink 10 or more standard drinks per week, we believe a minimal relevant effect size to be a difference in means at follow-up of 3 standard drinks per week. Similarly, those who are included based on having one episode of heavy episodic drinking per month, a minimal relevant difference at follow-up would be 0.3 less episodes on average per month (or about 1 per 3 months). For physical activity, participants are included if they have less than approximately 60 min of MVPA per day, for which a mean difference at follow-up of 30 min per week (i.e., 5 min per day) would be a minimal effect size of importance in this group. Following the same reasoning as above, among those included based on eating less than 500 g of fruit and vegetables on average per day, we believe a minimal relevant effect size to be a difference in means of 0.5 portions per day (50 g per day). Among those included based on sugary drinks consumption (3 or more drinks per week), we believe that a mean difference of 2 drinks per week at follow-up represents a minimal effect size. Finally, for smoking, we rely on data from a text message smoking cessation which was evaluated among Swedish high school students, suggesting that we may expect approximately 10% less smokers in the intervention group.

Using the minimally relevant effect sizes described above, we conducted a Monte Carlo study to guide recruitment. The study was designed to identify the necessary number to recruit for each of the six outcomes in order to achieve a power of 80% at the 0.05 significance level. Recruitment will continue until each of the six outcomes have been powered (no more than 24 months). All assumed effects were allowed to vary during the Monte Carlo simulations, following a normal distribution with a standard deviation of 0.025.

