Based on attrition observed in a previous trial of a digital smoking cessation intervention in this population [61], we assumed 25% attrition to follow-up. We found that we will require 267 individuals for weekly alcohol consumption, 534 for heavy episodic drinking, 734 for sugary drinks, 334 for fruit and vegetables, 800 for MVPA, and 467 for smoking. Thus, we will recruit until all of these number have been achieved (or 24 months have passed). Using data from surveys on Swedish high school students’ health behaviour, we found that this will likely require the recruitment of 2000 students to the trial, although correlations among behaviours may reduce this overall number.

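### The exploratory protective-effects analysis asks about onset of a behaviour but contrasts all participants, including those who already have it

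*Protocol article*

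**What the plan says.** Entry is by any one of six behaviours. In Study setting, recruitment and eligibility: "Students will be included in the trial if they fulfil at least one of six conditions". For any single outcome the trial can therefore contain both participants with the behaviour and participants without it.

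The primary analyses use the first group. In Primary and secondary outcomes: "Analyses of primary outcomes will be conducted among those fulfilling the respective criteria for inclusion at baseline".

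The section Protective effects of the intervention, placed under Exploratory outcomes, recalls that restriction and notes that everyone receives the same multi-behaviour programme. It reasons that "it is possible that the intervention may protect participants from developing unhealthy behaviour". To examine this, it plans, outcome by outcome, to "contrast all participants in the intervention and control groups to assess if either group is more or less likely to develop unhealthy risk behaviours"; the time covered is that of the intervention. It does not restrict the contrast to those free of the behaviour at baseline, and it does not say whether the event is new onset or risk status at follow-up.

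The adjustment set in Primary and secondary outcomes does not fill the gap: "All models will be adjusted for sex, age, family’s economic situation, and mediator variables at baseline". Baseline status on the behaviour in question is not listed.

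**The concern.** Prevention is a question about people who do not yet have the behaviour. The section moves from the subset with the behaviour (primary analyses) to everybody, where the question calls for the complement of that subset. Everybody includes the primary analysis set, in which a treatment effect is expected.

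At stake is the meaning of a positive result. If the contrast picks up improvement among those who already had the behaviour, part of the primary result reappears as a preventive effect. The article has national dissemination in schools in view, and there a prevention claim is a separate message from a behaviour-change claim and needs its own evidence.

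**Working it through.** The article gives no figure for this analysis, so there is none to reproduce. The check takes the two possible codings of the outcome in turn.

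**Inputs from the article (Power calculations, Randomisation)**
- Required number for the smoking outcome: 467. Likely total recruitment: 2000.
- Attrition: "we assumed 25% attrition to follow-up". This gives 2000 × 0.75 = 1500 completers, or 750 per arm under 1:1 allocation.
- Expected effect among baseline smokers: about 10% fewer smokers, taken here as 10 percentage points.
- Significance level 0.05, taken as two-sided.

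**Assumptions, not in the article**
- Baseline smoking share 467/2000 = 0.2335. The 467 is a recruitment requirement, so this is a stand-in for a prevalence.
- Cessation of 8% (control) v 18% (intervention) among baseline smokers.
- Uptake of 2% among baseline non-smokers in both arms, so no preventive effect.

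**Coding A: risk status at follow-up, all participants**

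Proportion smoking = share × (1 − cessation) + (1 − share) × uptake.
- Control: 0.2335 × 0.92 + 0.7665 × 0.02 = 0.230
- Intervention: 0.2335 × 0.82 + 0.7665 × 0.02 = 0.207
- Difference: 2.3 points (that is, 0.10 × 0.2335); odds ratio 0.87
- Standard error: √(0.230 × 0.770/750 + 0.207 × 0.793/750) = 0.0213
- Chance of significance: Φ(0.02335/0.0213 − 1.96) ≈ 0.19

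The whole difference comes from baseline smokers.

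Sensitivity: with control smoking at follow-up of 70% to 90% among baseline smokers and uptake of 1% to 5%, the chance of significance in that direction is about 18% to 23%. If the arms happen to be exactly balanced on baseline smokers, simulation gives about 4% to 15%; the expected 2.3-point difference is unchanged. Restricted to the roughly 1150 baseline non-smokers followed up (1500 − 467 × 0.75), the expected difference is 0 and the simulated rejection rate is 4.2% to 5.1%, close to nominal.

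The spurious difference grows with the share who already have the behaviour. The table assumes a 10-point effect in those with it, none in those without, and control rates at follow-up of 80% and 20% respectively, with 750 per arm.

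| Share with behaviour at baseline | Spurious difference | Chance of significance |
|---|---|---|
| 20% | 2.0 points | 13% |
| 40% | 4.0 points | 35% |
| 66.7% | 6.7 points | 74% |
| 80% | 8.0 points | 90% |

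**Coding B: new onset only, all participants**

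Those with the behaviour at baseline can never be events. Adding them to both arms leaves the expected risk ratio unchanged and multiplies the risk difference by the share at risk. With no preventive effect the rejection rate stays at about 5%. Power, with all onset rates assumed:

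| At risk per arm (of 750) | Onset, control v intervention | Power, restricted | Power, all participants |
|---|---|---|---|
| 575 | 5% v 2.5% | 61% | 60% |
| 575 | 10% v 6% | 71% | 70% |
| 250 | 20% v 12% | 69% | 63% |
| 250 | 40% v 30% | 65% | 52% |

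The loss is trivial when most participants are at risk and can be material when only a third are.

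**The case against.** The strongest reply is that the section names its event. It speaks of developing behaviours over the intervention period, which most naturally means onset. On that reading people who already have the behaviour cannot be events, their improvement cannot pass as prevention, and the cost is some dilution towards the null. The analysis is also exploratory, and a condensed article may leave coding and denominators to an analysis plan that is not shown.

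Much of this stands. A reader might infer that the plan will report a treatment effect as prevention, or that the analysis cannot answer its own question. The article supports neither as a certainty: the first follows only under coding A, and under coding B the analysis does answer the question, with some loss of precision. A reader might also take 23% as the protocol's expected smoking prevalence, or apply the two-thirds row to physical activity because the Summary says only one in three students meets the recommendation. But 467 and 2000 are recruitment numbers, and the Summary describes Swedish high school students generally, not a sample selected on risk behaviours.

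What does not stand is that this is only missing detail. The article does fix the population, as everybody, in explicit contrast to the primary subset. That population does not match the question under either coding, and the listed covariates do not condition on baseline status.

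**Conclusion.** The point holds as a mismatch between question and population in an exploratory analysis. As written, the contrast is contaminated by the primary treatment effect if the outcome is status at follow-up, or diluted if it is new onset.

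The smoking illustration (2.3 points, significant in about 19% of trials) is conditional on status at follow-up and on the assumed share, cessation and uptake; even then about four in five such trials would show nothing significant. Under new onset there is no false signal, and the power loss runs from about 1 point in the smoking-like example to 13 points in the least favourable example with a third at risk.

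The primary analyses have their own restriction, and the sample size does not depend on this analysis. Severity is minor.

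**What to change.** Add one clause to Protective effects of the intervention: for each primary outcome, include only participants who did not meet that outcome's entry criterion at baseline, and compare the randomised arms on meeting that criterion at follow-up.

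The cost is negligible. The baseline questionnaire already assesses every criterion, so the subset is defined by existing data. It is also defined before allocation, so the comparison remains a randomised one. Report the number at risk for each outcome, since it may be small where nearly all participants already have the behaviour.

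Each criterion must be scored the same way at both times. For heavy episodic drinking the eligibility section counts four or more drinks on one occasion, whereas the outcome section counts more than four, so those two definitions need to be reconciled first.

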#### Dosage-response

Data collected week-by-week in the intervention group may be useful to identify trends in potential behaviour change over time. Exploratory models will be created to identify patterns that are informative about intervention effects (such as plateaus). Similarly, we will regress primary outcomes on usage statistics in the intervention group, including frequency of use of different modules and whether or not the participant decided to stop the intervention before the end of the trial, possibly identifying a dose-effect relationship.

#### Heterogeneous treatment effects

Randomised controlled trials traditionally contrast two or more groups, however do not address individual variability (known as heterogenous treatment effects [60]). Some individuals may respond well to an intervention, while others might not, and some may be harmed - however contrasting two groups does not identify such individual level differences. To expand upon the effect modification analyses done in the primary analyses, we will explore prediction models which we will use to predict the outcome for each trial participant given both randomised conditions. Calibration will be assessed using cross-validation. The model will be used to predict how much each individual would benefit (or be harmed) by the novel intervention, and clustering will be used to identify groups of participants that are affected equally by the intervention. We will then explore similarities within each cluster of participants (for instance through multinomial regression) to identify which baseline characteristics are associated with benefit and harm of the intervention.

#### Power calculations

Considering the novelty of the intervention (digital multiple lifestyle) and the population (Swedish high school students), there are no existing full-scale trials from which an estimate of effects can be assumed. Also, as there are no interventions of this type available to high school students in Sweden, minimal relevant effect sizes were considered for this trial. We have based expected effect sizes on what we believe are minimally relevant for the population, and reasonable, given the target population and digital intervention context. For those included based on weekly alcohol consumption, who drink 10 or more standard drinks per week, we believe a minimal relevant effect size to be a difference in means at follow-up of 3 standard drinks per week. Similarly, those who are included based on having one episode of heavy episodic drinking per month, a minimal relevant difference at follow-up would be 0.3 less episodes on average per month (or about 1 per 3 months). For physical activity, participants are included if they have less than approximately 60 min of MVPA per day, for which a mean difference at follow-up of 30 min per week (i.e., 5 min per day) would be a minimal effect size of importance in this group. Following the same reasoning as above, among those included based on eating less than 500 g of fruit and vegetables on average per day, we believe a minimal relevant effect size to be a difference in means of 0.5 portions per day (50 g per day). Among those included based on sugary drinks consumption (3 or more drinks per week), we believe that a mean difference of 2 drinks per week at follow-up represents a minimal effect size. Finally, for smoking, we rely on data from a text message smoking cessation which was evaluated among Swedish high school students, suggesting that we may expect approximately 10% less smokers in the intervention group.

Using the minimally relevant effect sizes described above, we conducted a Monte Carlo study to guide recruitment. The study was designed to identify the necessary number to recruit for each of the six outcomes in order to achieve a power of 80% at the 0.05 significance level. Recruitment will continue until each of the six outcomes have been powered (no more than 24 months). All assumed effects were allowed to vary during the Monte Carlo simulations, following a normal distribution with a standard deviation of 0.025.

Based on attrition observed in a previous trial of a digital smoking cessation intervention in this population [61], we assumed 25% attrition to follow-up. We found that we will require 267 individuals for weekly alcohol consumption, 534 for heavy episodic drinking, 734 for sugary drinks, 334 for fruit and vegetables, 800 for MVPA, and 467 for smoking. Thus, we will recruit until all of these number have been achieved (or 24 months have passed). Using data from surveys on Swedish high school students’ health behaviour, we found that this will likely require the recruitment of 2000 students to the trial, although correlations among behaviours may reduce this overall number.

## Discussion

This study considers the “big four” health behaviours, i.e. alcohol, diet, physical activity, which all have a strong impact on health. As a growing body of research suggests that these health risk behaviours typically cluster and do not occur in isolation [21–23, 62], this trial can offer needed knowledge on the feasibility and effectiveness of an mHealth intervention targeting multiple behaviours, and to provide an mHealth platform where users can navigate freely using a personal dashboard that provides access to the four behaviour modules. The combination of recurring screening, text messages, and an interactive platform also mean a flexibility that encourage individual preferences. Findings in a systematic review and meta-analysis that evaluated the effectiveness of mHealth interventions targeting adolescents suggested that interventions using multiple mHealth solutions such as a combination of mobile applications, text messages and phone calls, have better potential than interventions that use single mode of delivery such as phone calls for instance. However, the results in the review was inconsistent between different outcomes which mean an uncertainty regarding the effectiveness of different mHealth solutions [63]. Therefore, the current study might contribute to the understanding of the effectiveness of interventions that use a combination of a mHealth solutions such as automatic text messages and interactive dashboard platforms.

